## Intervention description {11a}

### Exercise program

Both study groups will perform a standardized at-home exercise program, conducted three times per week. This program includes a combination of chair-stand exercises (part 1) and exercycle workouts (part 2), specifically tailored to suit the needs of older adults. To facilitate a uniform exercise experience and maintain consistency in the regimen, exercycles will be provided and set up in the participants’ homes.

Each exercise training day will commence with the chair-stand component (part 1), where participants are required to sit in a chair and then stand up as many times as possible within a 30-s timeframe. The 30CST forms part of the participants’ exercise program as well as provides practical application of the 30-Second Chair-Stand Test. The 30CST aims to enhance lower body strength and endurance, which are vital for daily activities and overall mobility.

Following the chair-stand exercise, participants will transition to using the exercycle (part 2). The exercycle workout is designed to improve cardiovascular fitness, leg strength, and overall endurance. This part of the exercise program is crucial for complementing the chair-stand activity, providing a balanced approach to muscle conditioning and aerobic exercise.

The following schedule of training will be completed by the participants each week from weeks 1 to 13. Day 1 of Week 1 must commence within 6 days of the Day 0 baseline visit.

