## Outcomes {12}

### Primary outcome

Our primary outcome is to evaluate the difference in the improvement of muscle performance, as measured by the 30-Second Chair-Stand Test (30CST), following a 13-week exercise regimen combined with weekly dosing of sirolimus (rapamycin) compared to exercise alone.

This assessment is crucial in establishing that the weekly administration of rapamycin, which inhibits the mechanistic target of the rapamycin (mTORC1) pathway, does not diminish the beneficial effects of exercise on muscle performance. While there is a potential for the sirolimus (rapamycin) group to exhibit a trend towards superiority in terms of exercise improvement, it is important to note that this study is not powered to conclusively determine superiority. Instead, our goal is to affirm that intermittent dosing of rapamycin alongside a regular exercise program will at least maintain, if not enhance, the muscle performance improvements that are typically observed with exercise alone in this demographic. This approach will provide valuable insights into the feasibility of incorporating rapamycin into exercise regimens for older adults, setting the stage for future studies that may be designed to explore the superiority of this combined intervention.

The rationale behind choosing the 30CST as our primary outcome measure lies in its relevance and sensitivity in assessing the functional muscle performance in older adults. By initiating an exercise regimen in participants who have not been regularly exercising—specifically, those not engaging in exercise that elevates heart rate for more than 15 min, three times a week—we anticipate observable improvements in muscle performance in the placebo group. This baseline improvement provides a critical comparative framework to evaluate the effects of rapamycin on exercise-induced muscle performance enhancements.

When measuring muscle performance, it is important to first define muscle strength, muscle power, and muscle endurance. Muscle strength refers to the amount of force a muscle can produce with a single maximal effort. Muscle power concerns work rate (work done per unit time) and is defined by the ability to exert a maximal force in as short a time as possible, as in accelerating, jumping, and throwing implements. Muscle endurance is the ability of muscles to exert force against resistance over a sustained period of time [30].

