**Table Tabd:** 

Age group	Mean	Standard deviation
60–69	14.0	2.4
70–79	12.9	3.0
80–89	11.9	3.6

We also have data on the change in the 30CST after exercise. A study of 20 healthy women aged between 65 and 79 demonstrated that after 12 weeks of a combined exercise intervention program with extra emphasis on balance and muscle strength found that the 30CST increased by 13.5% (14.8 ± 4 to 16.8 ± 3.4) [32]. A subsequent trial of 29 older adults included both males and females with an average age of 76 demonstrated a 20% improvement in the 30CST after a 12-week training program [33].

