Safety analysisSafety analysis set: this set includes all randomized participants. Adverse events will be allocated on an as-treated basis:◦ Events occurring before cessation of treatment or completion of the trial will be assigned to the randomized arm.◦ Events occurring after cessation will be assigned to the placebo arm.Analysis of adverse events:◦ Counts of adverse events will be regressed on the allocation arm as described above in interaction with the graded severity using negative binomial regression.◦ Dichotomized relatedness to the intervention (classified as possible, probable, or definite) will be regressed on the allocation arm using a quasi-binomial framework with logarithmic link (relative risk regression) or a relative risk working model (e.g., Poisson with bootstrap estimation of the variance) to test for non-inferiority of the rapamycin arm. Standard errors will be estimated using the bootstrap, resampling participants. The modalities of non-inferiority will be detailed in the final analysis plan.

Feasibility analysesScreening and randomization rates: overall and weekly screening and randomization rates will be reported with Poisson-based 95% confidence intervals.Cessation and withdrawal rates: rates of drug treatment cessation, exercise program cessation, and study withdrawal will be reported and compared across randomization arms using a log-rank test.Residual variance estimation: the residual variance of each outcome will be estimated to inform the sample size and analytical design of the phase 3 trial.

Adherence to medicationAdherence reporting: adherence to the medication will be reported by arm at 6 and 13 weeks using mean percentage of supply used and compared between arms using binomial regression with bootstrap-based standard errors and *p*-values [30].Causal effect estimation: the causal effect of the medication on the primary outcome will be estimated using two-stage residual inclusion estimation, with the randomized allocation as the instrumental variable [31].

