### Methods for additional analyses (e.g., subgroup analyses) {20b}

Subgroup analyses: subgroup analyses will be conducted to explore the potential differential effects of the intervention across various participant characteristics and to provide a more detailed understanding of the efficacy and safety of sirolimus (rapamycin) in conjunction with exercise. These additional analyses are not limited to the following:Age groups: participants will be stratified into age groups (65–74 and 75–85 years) to assess whether the intervention’s effectiveness varies with age.Gender: the impact of the intervention will be evaluated separately for male and female participants to identify any gender-specific effects.Baseline fitness levels: participants will be grouped based on their baseline fitness levels, as measured by the 30-Second Chair-Stand Test (30CST) and other baseline assessments, to determine if initial fitness influences the intervention’s outcomes.Adherence to protocol: Subgroup analyses will consider adherence levels, comparing outcomes between participants who adhered strictly to the exercise and medication regimen (≥75% adherence) and those with lower adherence.

Adjusted analyses: adjusted analyses will be performed to account for potential confounding factors and to provide a more accurate estimate of the intervention's effects.Baseline covariates: the primary and secondary outcome analyses will be adjusted for relevant baseline covariates, such as age, gender, baseline fitness levels, and any other significant factors identified during the blind review of the data.Generalized linear models (GLM): these models will be used to account for repeated measures and the correlation between baseline and follow-up assessments.

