### Methods in analysis to handle protocol non-adherence and any statistical methods to handle missing data {20c}

Definition of analysis populationsIntention-to-treat (ITT) analysis set: this set will be used for the primary analysis and includes all randomized participants analyzed according to their original assigned groups, regardless of protocol adherence.Per-protocol (PP) analysis set: this set will be used for sensitivity analyses and includes participants who complete at least 75% of the exercise sessions and take at least 75% of the protocol-stipulated doses of sirolimus (rapamycin) or placebo.

Handling protocol non-adherenceThe primary analysis will follow the ITT principle, which means all participants will be analyzed as randomized. This approach maintains the benefits of randomization by including all participants, regardless of adherence, and is appropriate for estimating the effect of treatment in a real-world setting.Sensitivity analyses using the PP set will help to understand the effect of the intervention among those who adhered to the protocol. This analysis will exclude participants who fail to meet the adherence criteria, providing insights into the efficacy of the intervention when administered as intended.

Statistical methods to handle missing dataMultiple imputation: missing data will be handled using multiple imputations, which helps to provide unbiased estimates by incorporating the uncertainty associated with missing data.Complete-case analysis: a complete-case analysis will be conducted, including only participants with no missing data, to compare and validate the results obtained from the multiple imputation method.Sensitivity analyses: sensitivity analyses will be conducted to assess the impact of different assumptions about the missing data. This may include:◦ Exploring the pattern and impact of missing data on the primary and secondary outcomes.◦ Comparing results from different imputation models to ensure robustness.

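### The adherence item in the subgroup list contrasts adherers with lower adherers, a non-randomised comparison expected to differ even if sirolimus has no effect

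*Protocol article*

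**What the plan says.** Methods for additional analyses {20b} opens with the purpose of the whole list: "subgroup analyses will be conducted to explore the potential differential effects of the intervention across various participant characteristics", so as to understand the efficacy and safety of sirolimus with exercise in more detail. Four items follow. The age and gender items ask how the effectiveness or impact of the intervention varies, and the baseline-fitness item asks whether initial fitness influences outcomes. The adherence item is defined differently, as "comparing outcomes between participants who adhered strictly to the exercise and medication regimen (≥75% adherence) and those with lower adherence".

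Four other parts of the article bear on it:

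- Exercise program (under Intervention description {11a}): "Both study groups will perform a standardized at-home exercise program, conducted three times per week". Each session begins with a 30-second chair stand, which is also the primary outcome task.
- Section {20c} uses the same 75% threshold for the per-protocol set, namely "participants who complete at least 75% of the exercise sessions and take at least 75% of the protocol-stipulated doses of sirolimus (rapamycin) or placebo". Placebo participants can therefore be adherent. The primary analysis is by intention to treat.
- Primary outcome (under Outcomes {12}): "we anticipate observable improvements in muscle performance in the placebo group". The article cites a 12-week exercise study in which the 30-Second Chair-Stand Test (30CST) rose from 14.8 (SD 4) to 16.8 (SD 3.4).
- Section {20a}, Adherence to medication, separately plans an estimate of the causal effect of the medication by "two-stage residual inclusion estimation, with the randomized allocation as the instrumental variable".

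**The concern.** Adherence is not a baseline characteristic. It is observed after randomisation and depends on health, motivation and tolerance of the programme, so participants who reach 75% of both components are self-selected. Part of what defines the group, the exercise, is itself expected to raise the outcome without any drug. Some of it is direct practice of the endpoint: 3 sessions × 13 weeks = 39 sessions, and 75% of 39 is 29.25, so an adherent participant has performed the chair stand in training at least 30 times.

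A contrast of adherers with lower adherers pools sirolimus and placebo participants on both sides, so randomisation does not protect it. It describes people who exercised and took capsules regularly against people who did not. The article nevertheless lists it among analyses of differential effects of the intervention, where a difference invites reading as evidence about sirolimus.

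**Working it through.** **Plan's own figure.** The article gives no expected size for this analysis. Its power figures (80% and 90% at d = 0.8 and 0.9) concern a comparison of arms of 20 and do not apply here.

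**Step 1: illustration by formula.** Suppose a latent normal adherence tendency has correlation *r* with the 13-week outcome, a share *p* is classed adherent, and there is no drug effect. The expected difference, in outcome SDs, is

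difference = *r* × φ(z_p) / [p(1 − p)],

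where φ is the standard normal density and z_p the cut-point.

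- *p* = 0.75: z = 0.674, φ = 0.318, p(1 − p) = 0.1875, factor 0.318 / 0.1875 = 1.69. For *r* = 0.1, 0.3 and 0.5 the difference is 0.17, 0.51 and 0.85 SD.
- *p* = 0.60: factor 0.386 / 0.24 = 1.61, giving 0.16 to 0.80 SD for *r* = 0.1 to 0.5.
- *p* = 0.85: factor 0.233 / 0.1275 = 1.83, giving 0.18 to 0.91 SD.

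Both *r* and *p* are assumptions. The assumed 75% share is a different quantity from the 75% adherence threshold.

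**Step 2: simulation with the sirolimus effect set to zero.** From the article: 20 per arm; baseline 14.8 (SD 4); follow-up SD 3.4; exercise gain in adherers 16.8 − 14.8 = 2.0 stands; nominal level 0.1, taken as two-sided. Assumed and varied: share adherent 60%, 75%, 85%; gain in lower adherers 2, 1 or 0 stands; extra prognostic advantage of adherers 0 or 1 stand. Assumed and fixed: baseline to follow-up correlation 0.6, and adherence independent of arm. The model is linear and adjusted for baseline, with 5,000 runs per scenario.

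Mean adherence contrast in stands, with the percentage of runs nominally significant:

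| Gain in lower adherers | Prognostic advantage | 60% adherent | 75% adherent | 85% adherent |
|---|---|---|---|---|
| 2 | 0 | 0.04 (10.6%) | −0.03 (9.2%) | 0.02 (9.8%) |
| 1 | 0 | 1.00 (29.0%) | 1.01 (25.6%) | 1.03 (21.5%) |
| 0 | 0 | 2.01 (69.9%) | 2.01 (60.5%) | 1.98 (47.0%) |
| 2 | 1 | 1.01 (29.5%) | 0.99 (24.6%) | 1.02 (20.7%) |
| 1 | 1 | 1.98 (68.9%) | 2.02 (62.0%) | 2.00 (49.2%) |

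In the same runs the randomised arm comparison averaged −0.03 to 0.02 stands and was significant in 9% to 11%. The arm-by-adherence interaction was also significant in 9% to 11%.

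**Step 3: reading.** The contrast is null only in the first row, where adherence is unrelated to both exercise benefit and prognosis. Elsewhere it is about 1 to 2 stands. Against an SD of 3.4 that is 1/3.4 = 0.29 to 2/3.4 = 0.59 SD, inside the range of step 1.

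**The case against.** The strongest reply is that the opening sentence of {20b} governs every item, so the adherence item may be meant as the arm effect within adherence strata, loosely worded in a condensed article. That reading is open. Under it the 0.17 to 0.85 SD would not arise, and the simulated interaction kept its nominal level. But the simulation made adherence independent of arm. If sirolimus affects adherence, for example through adverse events, strata formed after randomisation no longer preserve the randomised comparison. The sentence as written also compares outcomes between adherence groups and mentions no arm, so it needs correcting even if that was the intention.

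Other objections stand in part:

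- Adjustment for baseline outcome, age, gender and fitness would shrink the difference where adherence tracks those variables. It would not remove the part due to doing more exercise.
- The analysis is additional, the study is declared non-confirmatory, and testing is de-emphasised. This limits the consequence but does not make the contrast answer its stated question.
- The obvious substitutes have limits. The per-protocol comparison selects on the same 75% criterion, and the instrumental-variable estimate addresses medication only, not exercise adherence.

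Three stronger readings are tempting and not supported. A reader might infer that the contrast is bound to show an effect; the first row of the table shows that it need not. A reader might set the 0.17 to 0.85 SD beside the d = 0.8 in the Sample size section; that figure is for 20 against 20 by arm, whereas 75% adherent gives 30 against 10. A reader might say that the plan presents a dose-response analysis of sirolimus; it does not, since adherence is defined jointly by exercise and medication.

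**Conclusion.** The point holds, with modest consequence. As worded, the adherence item is a non-randomised contrast on a post-randomisation variable that includes exercise done by both arms. It cannot show a differential effect of sirolimus, and a difference is expected without any drug effect unless adherence is unrelated to both exercise benefit and prognosis. The article's own expectation that exercise alone improves the 30CST makes that exception implausible.

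The direction follows from the article; the size does not. The 0.17 to 0.85 SD and the 1 to 2 stands are illustrations that rest on the assumed share adherent, correlation, gain in lower adherers and prognostic advantage. The intention-to-treat primary analysis is untouched, so the main efficacy conclusion of the trial is not at risk from this item.

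**What to change.** Delete the adherence item from the subgroup list in {20b}. Alternatively, recast it as a descriptive, non-causal table of outcomes by adherence level within each arm, stating that it will not be used to infer an effect of sirolimus.

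For the medication-adherence question, point to the allocation-based two-stage residual inclusion estimate already in {20a}, and state that it does not address exercise adherence. Add to {20c} that the per-protocol arm comparison also conditions on adherence observed after randomisation and is supportive only. Adherence to medication by arm is already to be reported under {20a}.

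The cost is the loss or relabelling of one exploratory table and a few sentences of text. No data collection changes and no randomised comparison is lost.

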### Methods in analysis to handle protocol non-adherence and any statistical methods to handle missing data {20c}

Definition of analysis populationsIntention-to-treat (ITT) analysis set: this set will be used for the primary analysis and includes all randomized participants analyzed according to their original assigned groups, regardless of protocol adherence.Per-protocol (PP) analysis set: this set will be used for sensitivity analyses and includes participants who complete at least 75% of the exercise sessions and take at least 75% of the protocol-stipulated doses of sirolimus (rapamycin) or placebo.

Handling protocol non-adherenceThe primary analysis will follow the ITT principle, which means all participants will be analyzed as randomized. This approach maintains the benefits of randomization by including all participants, regardless of adherence, and is appropriate for estimating the effect of treatment in a real-world setting.Sensitivity analyses using the PP set will help to understand the effect of the intervention among those who adhered to the protocol. This analysis will exclude participants who fail to meet the adherence criteria, providing insights into the efficacy of the intervention when administered as intended.

Statistical methods to handle missing dataMultiple imputation: missing data will be handled using multiple imputations, which helps to provide unbiased estimates by incorporating the uncertainty associated with missing data.Complete-case analysis: a complete-case analysis will be conducted, including only participants with no missing data, to compare and validate the results obtained from the multiple imputation method.Sensitivity analyses: sensitivity analyses will be conducted to assess the impact of different assumptions about the missing data. This may include:◦ Exploring the pattern and impact of missing data on the primary and secondary outcomes.◦ Comparing results from different imputation models to ensure robustness.

Quality assurance for data collectionAll efforts will be made to minimize missing data. This includes training for study staff on accurate and complete data collection, regular monitoring, and data verification processes.Data queries will be generated to address missing or potentially erroneous data. Participants will be asked to provide another sample within a week if blood samples are lost or cannot be processed.Participants will be guided during weekly phone calls to complete their daily diaries accurately. Compliance will be reviewed at the interim visit (visit 3), and retraining will be provided as necessary.

### Plans to give access to the full protocol, participant level-data and statistical code {31c}

Access to full protocolThe full trial protocol will be made available to the public to ensure transparency and reproducibility of the research. It will be published as a supplementary document alongside the primary publication of the study results in a peer-reviewed journal.Additionally, the full protocol is accessible through the trial registry, Australia New Zealand Clinical Trials Registry (ANZCTR), under the registration number ACTRN12624000790549.

Access to participant-level dataParticipant-level data is anonymized to protect the privacy and confidentiality of study participants. Anonymized data sets will be made available to researchers upon reasonable request and after approval by the study’s sponsor.Requests for access to the participant-level data will need to include a detailed proposal outlining the research objectives and methods for data use. The proposal will be reviewed to ensure that it complies with ethical guidelines and data protection regulations.Access will be granted under a data-sharing agreement that stipulates the terms of use, including data protection measures and the requirement to acknowledge the original study.

Access to statistical codeThe statistical code used for data analysis will be made available to interested researchers to promote transparency and reproducibility. This will include scripts for data cleaning, analysis, and generation of results.The code will be shared through a public repository, such as GitHub or a similar platform, and linked in the primary publication of the study results.

Data management and confidentialitySource documents provide evidence for the existence of the participant and substantiate the integrity of the data collected. Source documents must be filed at the investigator’s site and may not be distributed to the sponsor should there be any risk of identifying any particular participant.Data reported on the electronic case report forms (eCRFs) that are transcribed from source documents must be consistent with the source documents or the discrepancies must be explained. All current medical records for participants must be available for review as part of study documentation. The investigator will describe documents comprising source documents prior to the study commencing by documenting these on the source document location list. This list must be maintained throughout the study, along with the source documentation, to support the data that have been entered into the eCRF.The sponsor or designee will perform monitoring to confirm that the data entered into the eCRF by authorized site personnel are accurate, complete, and verifiable from source documents; that the safety and rights of participants are being protected; and that the study is being conducted in accordance with the currently approved protocol and any other study agreements, ICH GCP, and Medsafe Guideline on the Regulation of Therapeutic Products in New Zealand Part 11.

